**Methods:**

A prospective, quantitative, experimental control study will be carried out in Reiyukai Eiko Masunaga Eye Hospital, located in Banepa, Kavrepalanchok, Nepal. All patients undergoing cataract surgery meeting the inclusion and exclusion criteria irrespective of the type of surgery (small-incision cataract surgery or phacoemulsification) will be included in the study. The patients will be randomly assigned to 1 of 2 groups. Patients in group 1 will be examined on day 1, day 7, and day 30, whereas patients in group 2 will be examined on day 1 and once between days 25 to 30. The minimum clinically important difference (MCID) in our study will be set according to the improvement in the Snellen visual acuity chart.

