### Sample Size and Sampling Technique

Sample size is calculated as follows: 2[Zα + Z1 – β] 2 × (sd2/d2) = 2 [1.96 + 1.645 ] 2 × [(0.1125)2/(0.025)2] = 263 for one group, where reference mean values for postoperative visual outcomes are taken from the study conducted by Deshpande et al [25]. The number of participants in intervention group will be 263 and the number of participants in the control (reference) group will be 263. We will use a random sampling technique and computer-generated random numbers to assign patients to the intervention or control group. We generated randomized numbers with a commonly used method [26]. The assignment will be done by the counsellor on the first postoperative day. The researchers will be masked as to randomization at all postoperative visits.

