## Results

More than 526 participants will be enrolled in the study, with a minimum of 263 assigned to the intervention group (deferred follow-up visits) and a minimum of 263 to the comparison group (standard practice of early postoperative follow-up visits). The sample will have diverse demographics, ensuring a representative population.

Visual acuity measurements will be obtained for both groups during the follow-up period. We will be able to statistically compute whether the deferred follow-up visit group demonstrates comparable visual acuity outcomes to the comparison group. This will be inferred if there are no statistically significant differences between the two groups in terms of visual acuity outcomes (*P*>.05).

Among the participants in the deferred follow-up visit group, the number of patients who experience postoperative complications during the 4-week follow-up period will be compared with the group with the 1-week follow up visit.

We will also determine if participants in the deferred follow-up visit group report high levels of satisfaction with the extended recovery period and reduced travel burden. The number of participants who express that deferring follow-up visits provided them with convenience and comfort during the recovery phase will be mentioned.

We will determine if reduction in early postoperative visits allows health care providers to allocate their time and expertise more efficiently, focusing on patients with immediate needs or complex postoperative care requirements.

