### Conclusion

The proposed study on deferring postoperative follow-up visits up to 4 weeks after uneventful cataract surgery in a tertiary level eye hospital in Kavrepalanchok will offer several potential benefits for patients, health care providers, and health care facilities. By prioritizing patient convenience, optimizing resource use, and ensuring appropriate support and education, this approach has the potential to improve access to care and overall patient satisfaction. However, careful consideration should be given to the selection criteria and establishment of effective communication channels to address potential challenges and ensure patient safety. The findings of this study will contribute valuable insights to the delivery of eye care services and may have implications for similar settings.

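### Satisfaction and convenience are to be reported for the deferred group only, so the result can describe acceptability but cannot show that deferral improves satisfaction

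*Protocol article*

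**What the plan says.** The Results section of the protocol article sets out what will be reported. On satisfaction, it will determine whether patients in the deferred group "report high levels of satisfaction with the extended recovery period and reduced travel burden". On convenience it says: "The number of participants who express that deferring follow-up visits provided them with convenience and comfort during the recovery phase will be mentioned". Both statements concern features of the schedule that only group 2 experiences.

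The same section treats its other results differently. Visual acuity is to be tested between the two groups, and the number of deferred patients with postoperative complications "will be compared with the group with the 1-week follow up visit".

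A randomised comparator exists. The abstract's Methods state: "The patients will be randomly assigned to 1 of 2 groups". The section on sample size gives the sizes: "The number of participants in intervention group will be 263 and the number of participants in the control (reference) group will be 263". Under Study Design, Setting, and Participants, both groups are told to attend at 1 month.

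The Discussion presents satisfaction as a likely gain. Expected Findings anticipates a positive effect on satisfaction and comfort, and the Conclusion says that "this approach has the potential to improve access to care and overall patient satisfaction". The section on data collection says that a questionnaire is still to be prepared and that counselors will ask the questions. No items are shown.

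**The concern.** Improvement is a comparative idea, and the planned satisfaction result has nothing to compare with. Suppose most deferred patients say that the schedule suited them. The reader would not know whether patients who also came at 1 week would rate their own schedule lower, the same or higher. Group 1 patients may have found the extra trip a burden, or they may have valued an early check. The planned count does not distinguish these cases.

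What is at stake is a supporting argument for changing practice. The Discussion uses satisfaction, with cost and resource use, to make the case for deferral. If the final report follows the plan as written, a high one-arm count could be read as evidence of a benefit that the data cannot estimate.

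**Working it through.** **The planned results side by side (Results section)**

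| Result | Group described | Between-group comparison stated? |
|---|---|---|
| Visual acuity | Both | Yes |
| Postoperative complications | Both | Yes |
| Satisfaction with the longer interval and less travel | Deferred only | No |
| Count finding deferral convenient and comfortable | Deferred only | No |

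The one-arm form is therefore stated in the text and is not a detail left to a fuller document. The effect of deferral on satisfaction is the rate in the deferred group minus the rate in the control group. With the second term not reported, the difference cannot be estimated at any sample size.

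**Precision of each form**

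The plan gives no figure for satisfaction, so there is none to reproduce. The inputs are:
- n = 263 per group, from the section on sample size.
- Proportion satisfied p. This is an assumption, with 50%, 80% and 90% shown.
- All 263 patients in each group answer, and p is the same in both groups.
- A yes/no split of the answer. The half-widths do not apply directly to a multi-point rating.

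One-arm half-width of the 95% interval: 1.96 × √[p(1 − p)/n].
- p = 0.80: 1.96 × √(0.16/263) = 0.048, or 4.8 points.

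Half-width for the between-group difference: 1.96 × √[2p(1 − p)/n].
- p = 0.50: 1.96 × √(2 × 0.25/263) = 0.085, or 8.5 points.
- p = 0.80: 1.96 × √(2 × 0.16/263) = 0.068, or 6.8 points.
- p = 0.90: 1.96 × √(2 × 0.09/263) = 0.051, or 5.1 points.

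The one-arm interval is narrower, but it describes a single group. The two-arm interval answers the comparative question with the patients already planned. Power for a 10-point difference (two-sided 5%) would be about 64% for 50% against 60%, 76% for 70% against 80%, and 90% for 80% against 90%.

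**A note on the 263**

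The printed sample-size formula for visual acuity does not give 263. It evaluates to 2 × (1.96 + 1.645)² × 0.1125²/0.025² = 2 × 12.996 × 20.25 = 526.3 per group; 263.2 results only without the leading 2. That is a separate matter. The figure of 263 is used here because it is the group size the article states. A larger group would only narrow the intervals.

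**The case against.** The strongest case on the other side is that the trial does not set out to show improved satisfaction. The Specific Objectives are visual outcome, safety and cost-benefit. The named primary outcome is visual acuity, and the named secondary outcome is the cost-benefit analysis. Describing how acceptable a new schedule is to those who received it is a legitimate one-arm aim, and the Discussion's statements are hedged as possibilities. This stands, and it limits the weight of the point. It does not remove it, because the Results section commits to reporting the count and the Discussion uses satisfaction to support deferral.

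A reader might also infer stronger faults that the article does not support:
- *That the questionnaire item is slanted.* No item is shown. The Results section describes what will be reported, not the words put to patients, so slanted wording is an inference.
- *That group 1 will never be asked.* The section on data collection does not restrict the questionnaire to one group. What the text establishes is that reporting is planned for the deferred group only.
- *That the count merely reflects satisfaction with the surgery.* The stated subject is the longer interval and the saved travel. Satisfaction with the operation may spill over into the answers, but the measure is specific to the schedule.
- *That an unfavourable result would be hidden.* The plan poses an open question, so a low count can be reported, and patients who did not endorse convenience can be found by subtraction. What is missing is the control group's view.

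**Conclusion.** The point holds in a limited form. As described, the satisfaction and convenience results can show how acceptable deferral was to the patients who had it. They cannot show that deferral improves satisfaction, or whether patients preferred to have a 1-week check. Asking both groups would estimate the difference to within about 6.8 points at 80% satisfied and 8.5 points at 50%, given a yes/no answer, complete response from 263 per group and assumed rates.

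The issue is minor to moderate. A reader might infer that it undermines the trial's main conclusion. It does not: the visual acuity, complication and cost results do not depend on it.

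**What to change.** In the questionnaire still to be prepared, ask both groups the same neutrally worded question at the 1-month visit about satisfaction with their own follow-up schedule, and a matching one about its convenience. Report the between-group difference with a 95% confidence interval. If a rating scale is used, state in advance which answers count as satisfied. Any count of patients who found deferral convenient can stay, labelled as descriptive of the deferred group and with no claim of improvement.

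The cost is one or two extra questions for group 1 at a visit already planned, and one extra secondary comparison. No added patients or visits are needed. One limit remains: the article has the counselor assign the group and counselors ask the questions, so the interviewer may know the allocation. A comparison between groups does not cure that, and the report should say so.

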## Discussion

### Expected Findings

The proposed study will investigate the feasibility and potential benefits of deferring postoperative follow-up visits up to 4 weeks after uneventful cataract surgery in a tertiary level eye hospital in Kavrepalanchok.

Deferring postoperative follow-up visits will allow patients to recover in the familiar environment of their homes, reducing the need for immediate travel and associated costs. This can have a positive impact on patient satisfaction and comfort during the recovery period. By avoiding unnecessary trips to the hospital, patients may experience reduced anxiety and stress, leading to an improved overall experience.

By spacing out follow-up visits, health care providers can optimize resource allocation within the tertiary level eye hospital. This approach will allow health care personnel to allocate their time and expertise more efficiently, focusing on patients who require immediate attention or complex postoperative care. Moreover, it can potentially reduce the burden on health care facilities, as fewer appointments are scheduled during the early postoperative period.

Deferring follow-up visits may also improve access to care, particularly for patients residing in remote areas. Traveling to health care facilities shortly after surgery can be challenging, especially for individuals with limited mobility or limited access to transportation. By extending the follow-up period, patients from distant locations can receive necessary care without the immediate need for travel, increasing the likelihood of their adherence to follow-up appointments.

One major concern related to deferring follow-up visits is the potential delay in detecting postoperative complications. Early postoperative visits allow health care providers to closely monitor patients for any signs of infection, inflammation, or other adverse events. When extending the follow-up period, it is crucial to educate patients regarding the signs and symptoms of postoperative complications so that they can visit the hospital, if required, on time. Patients should receive comprehensive information about self-care, potential warning signs, and instructions on when to seek medical attention. This will empower patients to actively participate in their own recovery and promote a sense of responsibility for their eye health.

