## Methods

### Study Design, Setting, and Participants

This will be a prospective, quantitative, experimental, noninferiority control study of health services use. Selected patients undergoing cataract surgery at Reiyukai Eiko Masunaga Eye Hospital irrespective of the type of surgery (SICS or phacoemulsification) will be included in the study.

All enrolled patients will undergo an examination on the first postoperative day conducted by an ophthalmologist who is unaware of the patient’s group assignment. Subsequently, the patient will proceed to the counselor’s office, where a unique identification number will be generated and the patient will be randomized into either group 1 or group 2.

In group 1, patients will be instructed to attend follow-up visits at 1 week and 1 month postoperatively. In group 2, patients will be instructed to attend a follow-up visit at 1 month postoperatively only. During the visit, the patients will receive detailed guidance on the appropriate use of medications and be educated about the signs and symptoms they should be vigilant for. The specific date of the postoperative visit will also be communicated.

At each follow-up visit, the patient will directly visit the counselor’s office. Upon arrival, they will be provided with a blank sheet of paper containing the unique identification number assigned to them on the first postoperative day. Visual acuity testing will be conducted by a blinded optometrist, while slit lamp biomicroscopy will be performed by a blinded ophthalmologist. Before leaving the hospital, the patient will return the paper to the counselor, who will then enter the necessary information into the patient’s file. 

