### Primary Outcome

Visual acuity measurements serve as the most important primary outcome. This includes assessing the level of visual improvement or stability achieved by patients during the 4-week follow-up period. Visual acuity outcomes can provide insights into the effectiveness of deferring follow-up visits for achieving comparable visual outcomes to the standard practice of early postoperative visits.

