### Secondary Outcome

The results of the cost-benefit analysis can be considered a secondary outcome. Conducting a cost-effectiveness analysis allows for the assessment of the economic implications and potential cost savings associated with deferring postoperative follow-up visits. This outcome provides insights into the financial feasibility and efficiency of implementing the deferred follow-up strategy.

We will perform a cost-benefit analysis to compare the economic status of the intervention group and active control group. For this we have to collect financial data on direct and indirect costs. Data on direct costs will be retrieved from the hospital record system, because this is the money paid directly by patients for their treatment after the surgery is recorded, including payments for consultation, medicine, and investigation (if required) at each follow-up visit.

Data on indirect costs, that is, costs incurred to the patient in the process of coming to the follow-up visit, include the following: (1) lost productivity costs (how much money the patient could have earned if the patient hadn’t come to the hospital follow-up visit), (2) transportation costs (the cost incurred while travelling), and (3) companion costs (patients will definitely have a companion, for whom we also have to calculate both costs above (lost productivity and transportation). Data on indirect costs will be obtained from interviews with the patients. We will calculate the average cost per visit, which will ultimately reveal the costs and benefits of the new approach, because the suggested new regimen will eliminate one follow-up visit.

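### Patients who miss follow-up are excluded after randomisation and no outcome compares attendance between arms, so the safety, adherence and access conclusions would rest on attenders only

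*Protocol article*

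**What the plan says.** Study Design, Setting, and Participants describes the trial as a "noninferiority control study of health services use". Under that section and Sample Size and Sampling Technique, the counsellor randomises patients on the first postoperative day. Group 1 is then asked to return at 1 week and 1 month, group 2 at 1 month only. Criterion 5 of the Exclusion Criteria excludes a patient who misses follow-up.

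The named outcomes are:
- Primary Outcome: "Visual acuity measurements serve as the most important primary outcome".
- Secondary Outcome: "The results of the cost-benefit analysis can be considered a secondary outcome".
- Results: for complications, "the number of patients who experience postoperative complications during the 4-week follow-up period will be compared" with the group that has the 1-week visit. The section also asks whether deferred patients "report high levels of satisfaction with the extended recovery period and reduced travel burden", and whether provider time is used more efficiently.

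Attendance is in none of these. The safety of deferral is the second specific objective, and the Abstract's Conclusions state the aim of showing that the 1-week visit can be deferred safely. Expected Findings suggests a benefit for patients living far away, "increasing the likelihood of their adherence to" follow-up appointments. The Conclusion adds that "this approach has the potential to improve access to care and overall patient satisfaction".

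**The concern.** Criterion 5 can only act after randomisation, because a patient has no follow-up visit to miss until the arm has been assigned. Read as written, it restricts the analysed set to people who attended. Two things follow.

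First, attendance cannot be studied in such a set, so the data could neither support nor contradict the remarks on adherence and access. Second, a deferred patient who misses the only scheduled visit drops out of both the acuity and the complication comparison, which are the evidence for safety.

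The Introduction itself treats attending follow-up on time as the way to deal with the two main causes of poor visual outcome, complications and uncorrected refractive error. The intervention alters the schedule through which that protection is delivered. Whether deferred patients are in fact examined again is thus part of the safety question. This is separate from bias in the acuity result: even if every randomised patient were kept for acuity, attendance by arm would still not be a planned comparison.

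**Working it through.** **Inputs.** The size is at least 263 per group (Sample Size and Sampling Technique; Results). Group 1 has two scheduled visits after day 1 and group 2 has one (Study Design, Setting, and Participants). The document gives no attendance or dropout rate, so the miss rate per visit, p, is an assumption and is shown over a range.

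**The plan's own figure.** There is none for attendance. The 263 is the stated size for acuity. The printed formula gives 2 × (1.96 + 1.645)² × (0.1125/0.025)² = 2 × 12.996 × 20.25 = 526.3 per group, so 263 does not reproduce. That is a separate matter. I use 263 below because it is the size the plan states.

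**Patients with no scheduled examination after day 1, if every patient is kept in the denominator.**
- Group 2: 263 × p.
- Group 1, misses independent within a patient: 263 × p².
- Group 1, misses fully dependent (whoever misses one visit misses both): 263 × p.

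| Assumed p | Group 2 | Group 1, independent | Group 1, fully dependent |
|---|---|---|---|
| 5% | 13.2 | 0.7 | 13.2 |
| 10% | 26.3 | 2.6 | 26.3 |
| 20% | 52.6 | 10.5 | 52.6 |
| 30% | 78.9 | 23.7 | 78.9 |

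Positively correlated misses lie between the two group 1 columns. If deferral halved the miss rate from 10% to 5%, group 2 would have 263 × 0.05 = 13.2, against 2.6 to 26.3 in group 1. The direction of the difference is then unknown as well as its size.

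**Would a count of exclusions do instead?** Criterion 5 does not say whether one missed visit in group 1 is enough. If it is, then at p = 10% with independent misses group 1 loses 263 × (1 − 0.9²) = 263 × 0.19 = 50.0 patients and group 2 loses 26.3. Yet those with no scheduled examination number 2.6 and 26.3. The two comparisons point in opposite directions, so the count of exclusions does not answer the coverage question.

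**Precision available.** With the same non-attendance rate in both arms, the 95% confidence interval half-width for the difference is 1.96 × √(2p(1 − p)/263). At p = 10% this is 1.96 × √(0.18/263) = 0.051. At 5%, 20% and 30% it is 3.7, 6.8 and 7.8 percentage points. Power at two-sided 0.05 with 263 per group is about 90% for 10% against 20%, but only 41% for 10% against 15%. The comparison would show a large difference and leave a small one open.

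**The case against.** Several counter-arguments have force.

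- A reader might infer that the protocol makes better adherence a hypothesis and then fails to test it. It does not. The remark is one hedged Discussion sentence about patients who live far away, the Conclusion speaks only of potential, and adherence is not among the specific objectives. The weight of the point must come from the safety objective and criterion 5.
- A reader might infer that only acuity and cost would be reported. The Results section also plans complications, satisfaction and provider time. That stands, but complications would still be counted among attenders only if criterion 5 is applied.
- A reader might infer that non-attendance would go unreported. Nothing says so. A participant flow diagram could show exclusions by arm, and an article commonly leaves that to fuller documents. What stands is that no comparison is planned, and that a bare count of exclusions can mislead, as shown above.
- A reader might infer a tenfold excess of unexamined patients in group 2 (26 against 2.6). That needs independent misses. Distance, mobility and transport, which the Discussion names, act on both visits and make misses correlated. With full dependence and equal rates the arms do not differ.
- A missed scheduled visit does not mean the patient is never seen. Patients are taught warning signs and may come unscheduled. The counts above are of scheduled examinations only.

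The remaining objection is that this is just part of the problem with criterion 5. Removing that criterion would make non-attendance visible, but would not by itself make it a planned result.

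**Conclusion.** The point holds in limited form. A stated rule removes non-attenders after randomisation, and none of the five kinds of outcome named is attendance. The safety conclusion and the hedged adherence and access statements would therefore rest on attenders, without a planned between-arm comparison of who attended. This goes beyond detail left to a fuller document, because the article lists its outcomes and fixes the rule.

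The size cannot be known from the document. At an assumed 10% miss rate per visit, about 26 of 263 group 2 patients would have no scheduled examination after day 1, against about 3 to 26 in group 1 according to how far misses cluster within patients. The document does not support a claim that deferral harms attendance, or that it helps. It should be changed before analysis, but it does not by itself invalidate the trial.

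**What to change.** Do not apply criterion 5 after randomisation for the outcomes below. Add two secondary outcomes, analysed by assigned arm in all randomised patients, each reported as a difference with a 95% confidence interval:

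- (a) Attended the 1-month visit. This is the measure of adherence.
- (b) Had at least one hospital-recorded examination after day 1, scheduled or unscheduled. This measures safety coverage. It is not a test of adherence, since group 1 has two scheduled opportunities and group 2 has one.

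Make the safety, adherence and access conclusions conditional on these results.

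The cost is one extra table and the retrieval of unscheduled visits from the hospital record. Scheduled visits already begin at the counsellor's office, and the hospital system is already to be used for payments at follow-up visits. Care received elsewhere would not be captured, and the report should say so.
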